#### Data management and dissemination of results

Individuals’ data or other related information will be kept in a file located in the principal investigator’s office. The authorised study team will enter the information into the electronic database by using double-entry methods. The private personal information (e.g., ID number and telephone) will be hidden and restricted to the principal investigator. The electronic database will be unified and managed by the Shenzhen Nanshan Center for Chronic Disease Control. The results will be presented at scientific conferences as abstracts, oral presentations or posters. In addition, the results of the present study will be disseminated through publication in an international peer-reviewed journal.

#### Side effects and safety assessment

There are no side effects of 10 mg/d of lutein supplementation. An observed safe level (OSL) of 20 mg/d for lutein has been suggested [30]. There is no anticipated harm or compensation for participation in this study. If they feel uncomfortable, all participants can contact a research assistant at any time. All serious and non-serious adverse events or reactions involving capsule supplementation (or both) will be recorded by the research assistant. The allocated treatment may be performed without blinding or may be discontinued under special circumstances during the study if the investigator deems it necessary. If possible, the patients who discontinued or deviated from the protocol will be followed up regarding all endpoints.

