### Study procedures

#### Recruitment and screening

Table 1 provides the schedule for enrolment, intervention and follow-up. Participants will be recruited by placing advertisements on social media sites and community bulletin boards. Once a volunteer expresses initial interest in participating in the study, he or she will have face-to-face or telephone communication with the research assistant. Detailed information on the study trial, including the purpose, the methods of the intervention and duration, will be provided to the volunteers. If they are still interested in this project after careful consideration, the structured standardised screening questionnaire, which is based mainly on the inclusion and exclusion criteria for the study, will be used to assess the potential eligibility of the participants for the study. Potential participants who are found not to be eligible will be excluded at this stage. Eligible participants will be invited to attend a further screening visit, which will take place at the CHSC. First, informed consent will be obtained from all participants. Second, for safety assessments, liver and renal function will be evaluated by collecting fasting blood samples and spot urine samples. Third, the anthropometric index will be measured by the trained investigators.

**Table 1 Tab1:** Schedule for screening, intervention and follow-up (test visit)

	Screening (−4 week)	Test visit 1 (week 0)	Test visit 2 (week 6)	Test visit 3 (week 12)
Screening questionnaire	X			
Demographic data	X			
Medication, health status and any changes	X	X	X	X
Informed consent	X			
Height and weight	X	X	X	X
Waist circumference and hip circumference	X	X	X	X
Body composition (bioelectric impedance)	X	X	X	X
Blood pressure	X	X	X	X
Blood sample	X	X	X	X
Allocation		X		
Physical activity questionnaire		X	X	X
Mini-mental State Examination		X		X
24-h diet recall		X	X	X
Spot urine sample	X	X		X
Faecal sample		X		X
Provided supply of capsules		X	X	
Tablet count			X	X
Compliance assessment			X	X
Assess adverse reactions			X	X
Collect unused test product			X	X

**Table 2 Tab2:** Biological and anthropometric parameters analysed in the lutein supplementation study

	Variable	Screening (−4 week)	Test visit 1 (week 0)	Intermediate visit (week 6)	Test visit 2 (week 12)
Biological	TC	X	X	X	X
	TGs	X	X	X	X
	HDL-C	X	X	X	X
	LDL-C	X	X	X	X
	ALT	X	X	X	X
	AST	X	X	X	X
	Creatinine	X	X	X	X
	FBG	X	X	X	X
	Insulin	X	X	X	X
	Lutein	X	X	X	X
	RBP4		X		X
	Adiponectin		X		X
	IL-6		X		X

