#### Biological sampling

At baseline and the middle and end of the trial, 12 mL of venous blood sample (4 mL in EDTA-coated sterile tubes and 8 mL in regular tubes) will be collected after the participants fast overnight. Table 2 summarises all the blood markers that are examined during the study. In addition to the indexes of liver and renal function (alanine aminotransferase (ALT), AST and creatinine), blood glucose, insulin, the lipid profile (TC, TGs, high-density lipoprotein cholesterol (HDL-C) and LDL-C) and CRP will be tested on the day of blood collection. Enzymatic methods (Biosino Biotechnology Company Ltd., Beijing, China) will be used for measuring serum hepatic enzymes, including ALT and AST. Serum creatinine will be determined by using the Jaffe method. Insulin concentrations (μU/mL) will be measured with a chemiluminescence microparticle immunoassay, high-sensitive CRP will be measured by using the immunoturbidimetry assay, and fasting blood glucose (mmol/L) will be measured by using the enzymatic colorimetric method with glucose oxidase using a commercially available kit. IR will be estimated by the homeostasis model assessment of insulin resistance (HOMA-IR): fasting insulin (μU/mL)*(fasting glucose (mmol/L)/22.5) [24]. The lipid profile will be determined by colorimetric methods using commercial kits (Biosino Biotechnology Company Ltd.) in a Hitachi 7080 automated analyser (Hitachi, Ltd., Tokyo, Japan). Serum lutein (μmol/L) will be analysed by high-performance liquid chromatography-tandem mass spectrometry. Retinol-binding protein 4 (RBP4) (μg/mL) and adiponectin (μg/mL) will be measured by using an enzyme-linked immunosorbent assay (ELISA) kit (Adipogen, San Diego, CA, USA). Serum levels of MCP-1, TNF-α, IL-6 and IL-1β will be measured by using the flow cytometry method (FCM).

Participants will be required to provide spot urine samples on the day of the screening and at test visit 1 and test visit 3. A routine urine test will be performed on the day of collection. Faecal samples will be collected at test visit 1 and visit 3 using a stool specimen collection kit, which includes the operating instructions, an ice pack, gloves, one sterile container and spoon, a sealed plastic pouch and a cool box. Participants will collect their faecal samples and bring them to the CHSC and then the samples will be transported and stored for further analysis.

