## Discussion

This study was designed to test the hypothesis that a lutein intervention will significantly modulate inflammatory factors and metabolic risk factors in people with central obesity compared with the effects observed in a control group receiving the placebo capsules. When this clinical study was designed, several key decisions were made to overcome the current limitations in the published literature. Previous studies on the antioxidant and anti-inflammatory properties of lutein focused mainly on the early atherosclerosis population [17, 31, 32]. However, as far as we are aware, well-controlled lutein supplementation is not common, and this study will be the only study of its type to be conducted in the context of central obesity. Central obesity is a state of chronic low-grade inflammation characterised by elevated concentrations of circulating inflammatory markers, which may be a critical link between metabolic disorders such as IR and diabetes [12, 33]. Therefore, individuals with central obesity also deserve attention.

Second, when focusing on central obesity, subjects with deficient lutein intake were considered. A larger body of research has indicated that dietary lutein intake or serum lutein levels (or both) are negatively associated with adiposity [22–24]. In addition, a previous longitudinal study found that obese subjects had lower concentrations of total carotenoids (including lutein) than subjects with a BMI of less than 22 kg/m^2^ [34]. These results indicate that central obesity may require more antioxidants to protect against oxidative stress and inflammation generated by adipose tissue.

However, we need to acknowledge that this clinical study has some limitations. First, the calculation of the dietary lutein intake is crude in the screening period and will be a reference for us to choose people who have a relatively lower intake. Second, this study will explore the short-term impact of the intervention because the participants will be treated for only 12 weeks. However, the development of metabolic diseases is a long and gradual process and can be influenced by other factors. Improvements in the inflammatory biomarkers and metabolic risk factors will not suggest that lutein intervention can prevent metabolic diseases; however, it can offer us a possibility for the prevention of inflammatory diseases. Whether lutein intervention can prevent metabolic diseases requires long-term intervention experiments.

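### The adverse-event rule can be read as covering only events attributed to the capsule, in a section that says lutein has no side effects, so harms may be under-recorded in both arms

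*Protocol article*

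**What the plan says.** Three statements in the protocol article bear on this point.

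- **Recording rule**, Side effects and safety assessment: "All serious and non-serious adverse events or reactions involving capsule supplementation (or both) will be recorded by the research assistant".
- **Expectation of harm**, same section: "There are no side effects of 10 mg/d of lutein supplementation", and "There is no anticipated harm or compensation for participation in this study". The support offered is a suggested observed safe level of 20 mg/d, with one reference. Participants also have a route for volunteering complaints: "If they feel uncomfortable, all participants can contact a research assistant at any time".
- **Schedule**, Table 1: the row "Assess adverse reactions" is marked at weeks 6 and 12. A separate row, "Medication, health status and any changes", is marked at screening and at weeks 0, 6 and 12.

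Table 2 adds ALT, AST and creatinine at screening and at weeks 0, 6 and 12. The Introduction calls reports on lutein in central obesity scarce. The Discussion says that, to the authors' knowledge, "this study will be the only study of its type to be conducted in the context of central obesity".

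**The concern.** An adverse event is anything untoward that happens during follow-up. A reaction is an event believed to be caused by the product. A blinded placebo-controlled trial measures harm best by recording every event in both arms and letting the comparison show any excess. If suspected cause decides whether an event is written down, some events never reach that comparison, and serious events thought unrelated could be among them.

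The recording sentence does not clearly rule this out, and the schedule uses the narrower word. Staff who take at face value the statement that there are no side effects would have little reason to link a complaint to the capsule. A low count of reactions could then partly reflect the recording rule and still be read as evidence of safety.

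**Working it through.** The plan gives no figure for harms to reproduce. The check is mainly one of wording, with a short calculation for scale.

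**1. Two readings of the recording rule.**

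| Reading | What the capsule phrase limits | What is recorded |
|---|---|---|
| Inclusive | reactions only | all serious and non-serious adverse events, plus capsule reactions |
| Narrow | events and reactions | only those linked to the capsule |

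The opening of the sentence favours the inclusive reading. The position of the phrase, after both nouns, allows the narrow one. The closing bracket fits either. The Discussion uses the same closing bracket for dietary intake and serum level, but no limiting phrase stands there, so that parallel does not settle which noun is limited here.

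**2. The schedule.** The Table 1 row names reactions, not events. Read with the rule, it fits the narrow reading at least as well as the inclusive one. Nothing in the article says that events are recorded whatever their suspected cause.

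**3. Whether other provisions fill the gap.**

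- The health-status row has a purpose stated under Test visit: to re-assess changes bearing on the eligibility criteria and decide whether the participant is still suitable. It may bring events to light, but it is not described as event recording.
- ALT, AST and creatinine cover liver and kidney function. They do not capture symptoms or clinical events.
- Contact at any time depends on the participant volunteering a complaint, which then falls under the same recording rule.

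**4. Effect of the narrow reading on the comparison.** Let the true risks be p_L (lutein) and p_P (placebo), and suppose a fraction c of events is recorded. Investigators, outcome assessors and patients are blinded (Randomisation and blinding), so take c as equal in the two arms.

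- Recorded risk difference: c·p_L − c·p_P = c(p_L − p_P), which is smaller than the true difference when c < 1.
- Recorded risk ratio: c·p_L / (c·p_P) = p_L / p_P, which is unchanged.

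The comparison survives with fewer events and less power to see an excess. The documents give no value for c, so no size can be put on the loss.

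**5. What a trial of this size could show with complete capture.** Recruitment of 120 at 1:1 gives 120/2 = 60 per arm.

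- If no event were seen among 60, the exact one-sided 95% upper limit solves (1 − p)^60 = 0.05: p = 1 − 0.05^(1/60) = 0.0487, or 4.9%.
- The chance of seeing at least one case among 60 is 1 − (1 − p)^60. For assumed true risks of 1%, 2% and 5% this is 45%, 70% and 95%.

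These figures assume that every event is captured and do not measure the wording problem. They show that this trial could not by itself establish the absence of side effects, and that it has few events to spare.

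**The case against.** The strongest reply is that the sentence begins with all serious and non-serious adverse events, and that its natural meaning is all events, plus reactions to the capsule. On that meaning there is no filter. The article also provides scheduled enquiries, repeated laboratory tests, a contact route, an independent monitor and blinding. Definitions and procedures for adverse events are often left to the full protocol.

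Much of this stands. The inclusive reading is available and may be the intended one. Missing definitions, the wording of the enquiry and the procedure for assessing relatedness are not defects in an article. What remains is that a rule the article does state can be followed in two ways, and the other provisions do not say which.

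A reader might also infer more than the text supports:

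- **That the research assistant judges causality.** The text says only that this person records. A judgement is implied only on the narrow reading, and nobody is assigned to make it.
- **That harms will be under-recorded.** This requires the narrow reading to be the one used, which the documents do not show.
- **That the comparison between arms is lost.** Under blinding, a filter should act alike in both arms. It removes events but leaves the comparison.
- **That the authors call the population unstudied.** They say reports are scarce. Their statement about the only study of its type is qualified, and it follows a remark on antioxidant and anti-inflammatory work, not on safety.
- **That the trial plans to conclude there are no side effects.** That sentence is background, and harms are not listed under Study outcomes.

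**Conclusion.** The point holds as a wording fault with a practical consequence. The recording rule can be followed as capsule-attributed recording, and the Table 1 label points the same way. The accompanying statement of no side effects goes further than its stated support: an observed safe level is a level at which no harm was seen, which is not proof that there is none. The cited source was not available, so this judgement rests on how the article describes it.

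If sites use the narrow reading, the trial may under-record harms in both arms, with smaller absolute differences and less power to see them. If they use the inclusive reading, nothing is lost. The size is therefore unknown. The 4.9% limit is context only and rests on 60 participants on lutein, complete follow-up and no events seen. The change is worth making because it is cheap and the Trial status section describes recruitment as open.

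**What to change.** 1. In Side effects and safety assessment, state that all serious and non-serious adverse events from allocation to week 12 are recorded in both arms, whatever their suspected cause. Make relatedness to the capsule a separate item, and say that counts will be reported by arm.
2. Relabel the Table 1 row at weeks 6 and 12 so that it refers to adverse events.
3. Replace the flat statement of no side effects with one limited to what the cited source observed at the level it studied.
4. Since recruitment had begun, confirm with the site which reading has been used so far, so that any events left out can be identified.

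The week 12 limit keeps the comparison clean, because the Test visit section offers lutein to the placebo group after the last visit.

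The cost is a change to protocol and form wording at visits that already exist, plus more entries to record and classify for 120 participants. No outcome, sample size or visit changes.

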### Statistical analysis

Two populations will be used in the analyses. The intention-to-treat (ITT) population will include all participants who have been randomly assigned, whereas the per-protocol (PP) population will include all participants who accomplish the entire intervention. The baseline characteristics of the study will be summarised as the means ± standard deviations for parametrically distributed data, geometric mean values (and 95% confidence intervals) for non-parametrically distributed data, and numbers (percentages) for categorical data.

Differences between participants who complete and withdraw from the trial will be analysed by using an independent *t* test or the Mann–Whitney test for continuous variables (e.g., age) and the chi-squared test for categorical variables (e.g., sex). For primary and secondary outcomes, analysis of covariance will be used to examine differences between lutein supplement and placebo at 12 weeks, adjusting for potential confounding factors and effect modifiers (e.g., baseline age and sex). The present study has no plan for subgroup analysis. Our statistical analysis will be performed by using R software, and the results will be considered significant at a *P* value of less than 0.05.

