### Study participants and eligibility criteria

It is estimated that 52 participants per treatment group would be required for 80% power and a 5% level of significance to detect the change in serum TGs over 12 weeks of supplementation [27]. Allowing for a dropout rate of about 15%, we aim to recruit 120 participants in total. Participants were eligible for this study if they fulfilled the following criteria: (1) age between 18 and 60 years, (2) waist circumference (WC) of at least 90 cm for males and at least 85 cm for females, (3) deficient lutein intake (dietary lutein intake of less than 10 mg/d), and (4) willingness to sign the informed consent form. People meeting any of the following criteria will be excluded from participation: (1) use of lutein supplementation or related health-care products within 1 month, (2) use of antibiotics within 1 month, (3) secondary obesity, (4) adoption of a special diet or meal replacement in the previous 2 weeks, (5) use of insulin or insulin sensitizers within 1 month, (6) chronic diseases (including type 2 diabetes, hypertension and dyslipidaemia) for over 10 years, (7) hepatorenal dysfunction (creatinine of more than 1.2 times the upper normal limit of creatinine, aspartate aminotransferase (AST) of more than 1 time the upper normal limit), (8) any active tumours/cancers, (9) regular use of drugs affecting blood lipid, (10) pregnancy or lactation or (11) history of gastrointestinal surgical operation.

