#### Study outcomes

The primary outcome consists of changes in the inflammatory biomarkers between the intervention and placebo group from baseline (test visit 1) to 12 weeks later (test visit 2). The secondary objectives are to assess changes in the anthropometric indexes, including weight, WC, HC and body composition.

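### The week-12 ANCOVA leaves out randomised participants without a week-12 value and makes no use of the week-6 secondary outcome data; a repeated-measures model suits those outcomes better

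*Protocol article*

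**What the plan says.** The Statistical analysis section sets two populations. For the first, "The intention-to-treat (ITT) population will include all participants who have been randomly assigned". For the second, "the per-protocol (PP) population will include all participants who accomplish the entire intervention". One method then serves both primary and secondary outcomes: "analysis of covariance will be used to examine differences between lutein supplement and placebo at 12 weeks", adjusted for covariates of which age and sex are given as examples.

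On withdrawals, the same section says only that "Differences between participants who complete and withdraw from the trial will be analysed", by t test, Mann–Whitney or chi-squared test.

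The sample size paragraph (Study participants and eligibility criteria) states: "Allowing for a dropout rate of about 15%, we aim to recruit 120 participants in total". The safety section adds: "If possible, the patients who discontinued or deviated from the protocol will be followed up regarding all endpoints".

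On timing, Study outcomes defines the primary result thus: "The primary outcome consists of changes in the inflammatory biomarkers between the intervention and placebo group from baseline" to 12 weeks. Table 2 schedules IL-6, IL-1β, CRP, MCP-1 and TNF-α at weeks 0 and 12 only. The secondary outcomes are weight, waist circumference (WC), hip circumference (HC) and body composition. Table 1 schedules all four at screening and at weeks 0, 6 and 12.

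**The concern.** A single-time-point ANCOVA needs a response at that time point. A participant who leaves before week 12 has none, so, unless values are imputed, the model does not cover the population it is meant to analyse. The per-protocol set does not contain these people either, so agreement between the two analyses would say nothing about those lost. Comparing the characteristics of completers and withdrawers describes who left but does not bring them into the treatment contrast.

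For the secondary outcomes the loss is partly avoidable. Someone who attends week 6 and leaves afterwards has already supplied half the trajectory, and the named analysis discards it. If leaving is related to progress by week 6, and differently in the two arms, the week-12 contrast is biased, and a model that includes week 6 removes the part of the bias that week 6 explains.

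**Working it through.** **Recruitment figure.** Inputs are 52 per arm, 1:1 allocation and about 15% dropout, all from the article. 2 × 52 = 104. Multiplying, 104 × 1.15 = 119.6, which rounds to the stated 120. Dividing, 104 / 0.85 = 122.4, or 123. The stated figure is reproduced by the first route and is close by the second.

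**Participants without a week-12 value.** 0.15 × 120 = 18, leaving 120 × 0.85 = 102, or 51 per arm. This is an upper figure, because some who stop capsules may still be measured at week 12.

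**Power is not the issue.** The article gives no effect size. Back-solving 52 per arm at two-sided 5% (sidedness assumed) and 80% power gives (1.960 + 0.842) × √(2/52) = 0.55 SD. At that difference, power is 79.2% with 51 per arm against 80.0% with 52, a loss of under one point.

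**Possible bias, by simulation.** These inputs are assumptions, not figures from the article:
- three-visit normal data with no true effect;
- 60 per arm, 9 lost per arm, all after week 6;
- correlation of baseline with follow-up 0.5 to 0.9, and of week 6 with week 12 0.6 to 0.95;
- an ANCOVA adjusted for the baseline value of the outcome.

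Dropout follows a score with a set correlation with the week 0 to 6 change. Settings with strong or random loss used 4,000 trials each; the other two used 2,000.

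| Dropout pattern | ANCOVA bias (SD) | Two-sided type I error |
|---|---|---|
| Random in both arms | about 0 | 4.3% to 5.4% |
| Correlation about 0.7, both arms alike | about 0 | 4.8% to 6.0% |
| Correlation 0.3 in lutein arm, random in placebo | about 0.03 | 4.6% to 5.6% |
| Correlation about 0.7 in lutein arm, random in placebo | 0.06 to 0.07 | 6.8% to 11.0% |

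Bias in the last two rows favours lutein. A second run of the last row with 3,000 trials per setting gave 0.061 to 0.079 SD and 6.4% to 11.3%.

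Detail of the last row, against a likelihood estimate that also uses week 6:

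| Correlations (baseline; week 6 with 12) | ANCOVA mean / SD of estimate | Bias ÷ SD | Likelihood mean / SD of estimate |
|---|---|---|---|
| 0.5; 0.6 | −0.068 / 0.173 | 0.39 | 0.000 / 0.170 |
| 0.6; 0.7 | −0.072 / 0.159 | 0.45 | 0.002 / 0.158 |
| 0.85; 0.9 | −0.060 / 0.106 | 0.57 | 0.001 / 0.103 |
| 0.9; 0.95 | −0.060 / 0.085 | 0.71 | 0.000 / 0.082 |

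The likelihood estimate is unbiased here and slightly more precise. With random loss both are unbiased. Two limits apply. The zero bias follows from making loss depend on an observed week-6 change, and participants lost before week 6 would gain less.

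**Which outcomes this reaches.** The simulation needs a week-6 value of the same variable. Tables 1 and 2 supply one for weight, WC, HC and body composition. They supply none for the inflammatory markers.

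**The case against.** The strongest objection is that a journal article may leave missing-data rules to a fuller document, and that ANCOVA can be fitted to imputed data. ITT as all randomised and ANCOVA as the method do not contradict each other. That stands: the absence of an imputation rule is not an error. What remains is a choice the article does make, a week-12 analysis of outcomes that are also measured at week 6, where a better method is available at almost no cost.

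Three stronger readings are tempting and are not supported.

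- *The ITT result becomes a completer result, identical to per protocol.* The safety section intends to follow discontinuers for all endpoints where possible. Anyone so followed belongs in ITT and may be outside per protocol, so the two sets need not coincide.
- *Week-6 data on the primary outcome are being ignored.* Table 2 plans none for the inflammatory markers. A three-visit model cannot be applied to them as scheduled, and nothing here justifies an additional assay run.
- *The article contradicts itself on week-6 CRP.* Biological sampling describes blood draws at baseline, middle and end, and lists several tests, "and CRP will be tested on the day of blood collection". This reads as assay timing. The same section refers to Table 2 for the markers, and Table 2 gives CRP at weeks 0 and 12. The two can be read together.

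The size of the bias is also open to challenge. Nothing in the article suggests that dropout would depend strongly on response in one arm and not in the other, and participants are blinded with identical capsules. The upper figures are therefore a worst case. Even 0.07 SD is about one-eighth of the 0.55 SD implied by the sample size (0.07 / 0.55 = 0.13).

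**Conclusion.** The point holds in a limited form. As written, the only treatment comparison omits randomised participants without a week-12 value, up to about 18 of 120, and makes no use of the week-6 secondary outcome data.

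Under random loss, or a common mechanism in both arms, the bias is about nil. Weak one-arm dependence gives about 0.03 SD, with type I error under 6% in the runs. Only strong one-arm dependence gives 0.06 to 0.07 SD and about 6% to 11%. These figures rest on the assumed dropout patterns and correlations, and on all loss occurring after week 6.

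The case for change does not need the worst case: for the secondary outcomes, the repeated-measures model was at least as precise in every setting compared. For the primary outcome the point reduces to how participants without a week-12 value enter the analysis, or what the result is called.

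**What to change.** **Secondary outcomes (weight, WC, HC, body composition).** In Statistical analysis, replace the week-12 ANCOVA in the ITT population with a mixed model for repeated measures on weeks 0, 6 and 12, with arm-by-visit terms, unstructured covariance and the covariates already planned. The week-12 lutein minus placebo contrast is the estimate. Constrain the week-0 means to be equal in the two arms, or enter the week-0 value as a covariate, so that the contrast stays adjusted for baseline; the precision comparison above assumes this.

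**Primary outcome (inflammatory markers).** Keep the ANCOVA. Either impute missing week-12 values by arm from baseline and the other measures taken at week 6, or describe the result as an analysis of participants with week-12 data. The gain from imputation was not simulated and should not be assumed to match that for the secondary outcomes.

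**Cost.** Revised wording and a little programming in R. No extra visits, participants or assays.

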**Methods:**

This study will be conducted as a double-blind, parallel placebo-controlled clinical trial in which 120 people who have central obesity, are 18 to 60 years old and are willing to provide informed consent will be randomly assigned to the intervention or placebo group in a 1:1 ratio according to sex, age and waist circumference. The intervention group will receive 10 mg daily lutein supplementation for 12 weeks to explore the effect of lutein supplementation on serum lutein, glycaemic and lipid profiles, inflammatory factors and body composition. Two populations (intention-to-treat population and per-protocol population) will be used in the data analyses.

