### Randomisation and blinding

After the inclusion and exclusion criteria are assessed and informed consent is obtained, participants will be allocated to the lutein group or the placebo group. Computer-generated random numbers will be used for allocation sequence generation and stratification will be completed according to sex, age and WC. This part of the study will be performed by a person who is operationally independent from the study team. Allocation concealment will be implemented by using a random number card in a black envelope. The details of the allocation will be concealed from the investigators, outcome assessors and the patients until all data collection is complete. The collected data of the patients will be kept confidential during this trial.

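### The ANCOVA covariate list names neither the week-0 value of the outcome nor waist circumference, so as written it does not secure precision that is available at no cost

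*Protocol article*

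**What the plan says.** Under Study outcomes, the primary outcome is defined as "changes in the inflammatory biomarkers between the intervention and placebo group from baseline (test visit 1) to 12 weeks later". Under Statistical analysis, "analysis of covariance will be used to examine differences between lutein supplement and placebo at 12 weeks", for primary and secondary outcomes alike, "adjusting for potential confounding factors and effect modifiers (e.g., baseline age and sex". The same section says that no subgroup analysis is planned.

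Under Randomisation and blinding, "stratification will be completed according to sex, age and WC"; the abstract repeats the three factors. Table 2 schedules IL-6, IL-1β, CRP, MCP-1 and TNF-α at week 0 and week 12, and WC at screening and every visit. The baseline value of each inflammatory marker and baseline WC will therefore be in the database.

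**The concern.** Two variables that one would expect in this model are not named.

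- **The week-0 value of the outcome.** It is usually the strongest single predictor of the week-12 value. In the sentence on covariates, the word baseline is attached to age and sex, not to the biomarker. One section defines a change and the other compares arms at 12 weeks, so the text alone does not settle whether the estimate is a week-12 comparison, a change score or a baseline-adjusted difference.
- **WC.** It is one of three stratification factors and the only one not named. An analysis that ignores a prognostic stratification factor tends to give standard errors that are somewhat too large.

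The principle for choosing covariates also fits a randomised trial poorly. Confounding is a reason for adjustment in observational work; here covariates should be chosen because they predict the outcome or were used in the randomisation. An effect modifier entered as a main effect does not address modification. A list given only by example leaves the choice of covariates, and hence the P value, less constrained than it could be.

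What is at stake is precision and pre-specification, not validity.

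**Working it through.** **The plan's own figure.** Under Study participants and eligibility criteria, "It is estimated that 52 participants per treatment group would be required". The sizing endpoint is serum triglycerides, with power set at 80% and alpha at 5%. No difference or SD is given, so 52 cannot be reproduced. Working backwards with the normal approximation and an assumed two-sided test, the implied standardised difference is √(2/52) × (1.960 + 0.842) = 0.549. It belongs to triglycerides, not to the inflammatory markers, and the article does not say on which SD scale it was set.

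**Residual variance under three analyses.** Assume the same variance σ² at week 0 and week 12 and correlation rho between them. If age and sex are in all three models, read rho as the correlation remaining after that adjustment.

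- Week-12 value only: σ²
- Change score: 2σ²(1 − rho)
- ANCOVA with the baseline value: σ²(1 − rho²)

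The ratio of ANCOVA to week-12 only is 1 − rho². The ratio of ANCOVA to change score is (1 − rho²)/[2(1 − rho)] = (1 + rho)/2. The article gives no correlation, so a range is shown, in units of σ²:

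| Assumed rho | Week-12 only | Change score | ANCOVA with baseline | ANCOVA ÷ week-12 only | ANCOVA ÷ change score |
|---|---|---|---|---|---|
| 0.3 | 1.00 | 1.40 | 0.91 | 0.91 | 0.65 |
| 0.5 | 1.00 | 1.00 | 0.75 | 0.75 | 0.75 |
| 0.7 | 1.00 | 0.60 | 0.51 | 0.51 | 0.85 |

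Baseline-adjusted ANCOVA has the smallest variance in every row. At rho = 0.5 the reduction is 25% against either alternative, which is worth 1/0.75 = 1.33 times the participants.

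**Why this is not converted into a power claim.** Take 0.549 and 52 per arm purely as an illustration.

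- If 0.549 is in week-12 SD units, the week-12-only comparison has 80% power, and baseline-adjusted ANCOVA has 83.6%, 89.9% and 97.5% at rho = 0.3, 0.5 and 0.7.
- If 0.549 is in change-score SD units, the change score has 80% power, and ANCOVA has 93.5%, 89.9% and 86.0% at the same correlations.

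The trend across rho reverses with a scale that the article does not state. Only the variance ratios are secure.

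**WC.** If WC explains a further share R² of the residual variance, that variance falls by the factor 1 − R². For an assumed R² of 0.01 to 0.10 the factor is 0.99 to 0.90. From an 80% starting point at 52 per arm, power becomes 80.4% to 84.0%, a gain of about 0 to 4 points.

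**The case against.** The strongest reply is that age and sex are introduced as examples. Nothing in the article excludes the baseline value or WC. An ANCOVA of an outcome defined as a change from baseline is naturally read as including the baseline value, and a full covariate list is commonly left to the full protocol or SAP. This stands. A reader might infer that the trial will give up precision, or that the model contains age and sex only; the text supports neither. It supports only that the commitment is not made.

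A reader might also infer bias from chance baseline imbalance or regression to the mean. That does not follow. Under randomisation both the week-12 comparison and the change score are unbiased. Regression to the mean acts alike on both arms in expectation, participants are not selected on inflammatory markers, and chance imbalance is reflected in the standard error. Leaving out a stratification factor errs in the conservative direction.

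It is also fair to say that WC carries much less weight than the baseline value, and that a single model for all outcomes would enter WC twice when WC is itself the outcome, as it is among the secondary outcomes.

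The reply does not remove the point about what the article does state. The selection principle is written down and suits a randomised comparison poorly, and the examples match the randomisation only in part. Naming the baseline value and all three stratification factors is a better statement, and it uses data already scheduled.

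**Conclusion.** The point holds as a recommendation to improve precision and pre-specification. The article names two of the three stratification factors, does not name the week-0 value of the outcome, and leaves the list open.

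The benefit of securing baseline adjustment is a residual variance of 1 − rho² relative to a week-12-only comparison, or (1 + rho)/2 relative to a change score. Each is 25% lower at rho = 0.5. Over rho from 0.3 to 0.7, the reduction runs from 9% to 49% against week-12 only and from 35% to 15% against the change score. These figures assume equal variance at the two visits, and the correlation is itself an assumption. If the SAP already fixes baseline adjustment, the gain is already in hand and only the article's wording needs to change.

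No power figure for the inflammatory biomarkers can be stated. The contribution of WC is small, and its main justification is that the analysis should reflect the stratified randomisation. The documents do not support a claim of bias or of inflated type I error from leaving out these covariates.

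**What to change.** Replace the wording about potential confounders and effect modifiers, and its open list of examples, with a fixed main model:

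week-12 value = treatment + baseline (week-0) value of the same variable + sex + age + WC

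State whether age and WC enter as strata or as measured values. When WC is the outcome, enter baseline WC once only. With the baseline value in the model, the treatment estimate is the same whether the dependent variable is the week-12 value or the change, so the Study outcomes and Statistical analysis sections then describe the same comparison.

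The cost is one or two sentences. No participants, visits or assays are added, since every covariate is collected at or before week 0. The article reports recruitment as open and allocation as concealed until data collection is complete, so the model can be fixed before anyone sees results by arm.
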